### Analyses

#### Analysis of participants

The data collected will be screened for accuracy, missing data, outliers, and statistical assumptions. SAS Version 9.3 will be used for all statistical analyses. All statistical tests will be performed using two-sided tests at the 0.05 significance level. For all models, the results will be expressed as effects, standard errors, 95% confidence intervals, and associated *p* values. The evaluation will be conducted in accordance with the intention-to-treat principle; therefore, imputation (using multiple imputation) will be used to address missing data and compare these results with the complete case analysis. If there are discrepancies between the multiple imputation and complete case results, we will conduct a sensitivity analysis using different multiple imputation methods (appropriate for the pattern of missingness) to see how robust the analysis is for the chosen method(s) of handling missing data [85]. This procedure will result in multiple data sets and models being run on each data set. Appropriate methods will be used to combine the results to generate pooled parameter estimates, standard errors, and confidence limits.

An analysis of baseline (*T*1) data will be performed to compare the demographic and clinical characteristics of the intervention and control groups. This analysis will confirm whether the two groups are equal on these variables. Means and standard deviations will be generated for continuous variables, and frequencies and proportions for categorical variables. The appropriate significance test (e.g., *t* test for continuous measures, chi-square for categorical) will be applied to identify any significant differences between the groups. Significant differences will be adjusted for in the outcomes analyses.

For the analyses relating to clients, *t* tests will be used to compare the changes in primary and secondary outcomes from baseline (*T*
_1_) and 6 months (*T*
_2_) in the two groups. Primary and secondary measures will also be analyzed using repeated measures ANCOVA (two time periods) to understand the factors shaping these outcomes. Site will be included as a predictor, consistent with our randomization strategy which stratified by site. Other potential covariates include age, gender, self-efficacy, duration of diabetes, and level of comorbidity. Covariates will be identified and selected for inclusion in the models based on bivariate analyses to confirm their relationship with the outcome and the absence of a significant relationship with other covariates. We will conduct a cross-jurisdictional comparison across Ontario and Alberta, given the differences in community-based structures.

We will also examine the relationship between the dose of the intervention and the primary outcome variable (6-month PCS-12 score) in order to better understand the mechanisms underlying this outcome and to tease out quantity versus quality effects. Regression will be used and dose will be measured by the number of home visits and number of group sessions attended (explored as individual components and as a combined measure).

The effectiveness of an intervention is often dependent on the characteristics of the population; thus, this study will include a subgroup analysis to identify what clients benefit most from which approach to treatment [86]. A range of characteristics thought to influence self-management behavior will be evaluated, including: age, gender, duration of diabetes, depressive symptoms, number of comorbidities, self-efficacy and caregiver support. Regression using two-way interactions between the study group (intervention versus control) and each characteristic will be conducted to examine subgroup effects [87, 88]. The models will use the PCS-12 score for the dependent variable and independent variables will include group assignment, client characteristic (e.g., at least three versus less than three comorbidities), and the interaction term.

Regarding the family caregivers, data on their demographic characteristics and the three outcomes (HRQoL, depressive symptoms, and strain) will be collected at baseline and again at 6 months. Descriptive statistics will be generated to summarize the characteristics and outcomes for the family caregivers in each group, with *t* tests and chi-square tests being used to evaluate group differences in continuous and categorical variables, respectively.

Statistical procedures for interventionist outcomes are limited by the small number of individuals involved; therefore, descriptive analysis will be mainly used to report the results. We anticipate collecting 21 TCI assessments (baseline and 6 months), one for each of three members of the program team (RN, RD, PC) at each of the sites. We will attempt to explore potential site differences and relationships with key variables (e.g., dose of the intervention, primary and secondary outcomes of T2DM clients).

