### Sample size

The sample size for the RCT was calculated to detect a minimally important difference (MID) in the primary outcome measure (PCS-12). The developers suggest that the MID for interpretation of group mean PCS-12 score differences is approximately 3.0, which corresponds to an effect size of 0.30 [56]. However, the developers also acknowledge that this MID estimate is a matter of ongoing debate. Robust research on effect sizes seen across a range of studies using a variety of quality-of-life measures has shown that the mean effect size is remarkably consistent at 0.50, or half the standard deviation [57]. This effect size is close to the one observed in our pilot study, which was 0.40 [43].

We based our estimate of the sample size on an effect size of 0.50, 5% alpha, 80% power and 20% attrition (18% was observed in our pilot study). Using these assumptions, the sample size was 80 (each) for the intervention and control groups.

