### Randomization design

After providing written, informed consent and completing the baseline questionnaires, participants will be randomly assigned to either the intervention or the control arm of the study using a 1:1 allocation ratio. Stratified permuted block randomization will be used to assign participants to the control and intervention groups. Study sites are expected to be relatively homogeneous regarding client sociodemographic and clinical characteristics and the delivery of intervention and usual care services. However, to minimize the confounding effects of possible differences among the study sites, the sites will be used as a stratum. The randomized sequence at each site will be based on assignments of blocks randomly selected from sizes of 2, 4, or 6. A biostatistician not involved in the recruitment process will generate the random number assignments for each site using SAS Version 9.3. Random number sequences will be input into a centralized web-based randomization service (REDCap) that will allocate clients to the control or intervention group at each site in accordance with the sequence.

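### Adjusting for baseline variables that happen to differ significantly, and screening covariates on outcome data, lets chance pick the treatment-effect model and can leave out prognostic variables

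*Protocol article*

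**What the plan says.** All references are to the protocol article.

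- **Baseline tests.** Under Analysis of participants, demographic and clinical variables are compared between arms with t or chi-square tests. The stated purpose is: "This analysis will confirm whether the two groups are equal on these variables". The consequence is: "Significant differences will be adjusted for in the outcomes analyses". The general level applies: "All statistical tests will be performed using two-sided tests at the 0.05 significance level".
- **Main comparison.** The same section and Table 2 put first a t test comparing change from baseline to 6 months between the groups. No covariate is named for it.
- **ANCOVA.** Primary and secondary measures also go through a repeated-measures ANCOVA. Site is fixed as a predictor. Beyond that, "Other potential covariates include age, gender, self-efficacy, duration of diabetes, and level of comorbidity", and the selection rule is: "Covariates will be identified and selected for inclusion in the models based on bivariate analyses to confirm their relationship with the outcome". A second condition requires that a covariate have no significant relation to the other covariates. Table 2 describes this ANCOVA as exploring predictors of the primary outcome.
- **Allocation.** Participants are "randomly assigned to either the intervention or the control arm of the study using a 1:1 allocation ratio", by computer-generated permuted blocks within site.

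**The concern.** There are two data-driven rules, and both can reach the estimate of the treatment effect.

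The baseline-test rule asks a question that randomization has already answered. If allocation was sound, every baseline difference is chance, so a test cannot confirm equality. A significant result does not show that the variable predicts PCS-12, and a non-significant one does not show that it can be ignored. The rule covers the outcome analyses without exception, yet a two-sample t test cannot carry an adjustment. If a variable is flagged, the article does not say which model then gives the treatment effect.

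The ANCOVA screen cannot be applied until outcomes are known. Its second condition works against variables that are related to each other, as age, diabetes duration and comorbidity plausibly are. The two rules can also disagree. A variable that is imbalanced but unrelated to the outcome, or correlated with another covariate, is in under the first rule and out under the second, and no precedence is given.

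At stake are the credibility of an effect model chosen after the data are seen, and the precision that a fixed set of prognostic covariates would bring.

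**Working it through.** **1. The plan's own sample size.** Inputs from Sample size: "an effect size of 0.50, 5% alpha, 80% power and 20% attrition". The normal formula is n = 2(1.96 + 0.8416)²/0.50² = 62.8, so 63 per arm, and 63/0.8 = 78.75, so 79. The t-based calculation gives 63.8, so 64, and 64/0.8 = 80. This matches "the sample size was 80 (each) for the intervention and control groups". The figure is sound, and 64 completers per arm is used below.

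**2. How often chance changes the model.** Each baseline test is significant with probability 0.05. For k independent tests, P(at least one) = 1 − 0.95^k. The article does not state k, so a range is shown.

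| k | P(at least one variable flagged) |
|---|---|
| 5 | 22.6% |
| 10 | 40.1% |
| 15 | 53.7% |
| 20 | 64.2% |

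Any particular variable is flagged 5% of the time, so a prognostic covariate is omitted about 95% of the time, whatever its strength.

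**3. Simulation of both rules.** 64 completers per arm; five equally correlated normal covariates, one of them prognostic; 2,000 runs per scenario; true effect 0.50 SD. The correlations are assumptions. The screen is read strictly: p < 0.05 with the outcome and p ≥ 0.05 with every other candidate.

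| Prognostic r | Correlation between covariates | Screen drops the prognostic covariate | Power, unadjusted | Power, baseline-test rule | Power, screen | Power, all five fixed |
|---|---|---|---|---|---|---|
| 0.3 | 0 | 25.0% | 0.795 | 0.791 | 0.811 | 0.807 |
| 0.3 | 0.2 | 95.8% | 0.814 | 0.813 | 0.814 | 0.830 |
| 0.3 | 0.3 | 100% | 0.812 | 0.812 | 0.812 | 0.840 |
| 0.5 | 0 | 18.5% | 0.799 | 0.804 | 0.875 | 0.887 |
| 0.5 | 0.2 | 95.2% | 0.803 | 0.810 | 0.805 | 0.890 |
| 0.5 | 0.3 | 99.9% | 0.802 | 0.817 | 0.802 | 0.884 |

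The simulation error of one power figure is about √(0.8 × 0.2/2000) = 0.009, so gaps of a point or so mean little. With no true effect, rejection rates under the baseline-test rule, the screen, or both combined ran from 0.039 to 0.051.

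**4. Analytic check of the precision at stake.** If fixed covariates explain a share R² of the outcome variance, power ≈ Φ(d√(n/2)/√(1 − R²) − 1.96), with √(64/2) = 5.657.

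- d = 0.50 (design value): R² = 0 gives Φ(0.868) = 0.81. R² = 0.3² = 0.09 gives Φ(1.005) = 0.84. R² = 0.5² = 0.25 gives Φ(1.306) = 0.90.
- d = 0.40 (pilot effect quoted in Sample size): R² = 0 gives Φ(0.303) = 0.62. R² = 0.09 gives Φ(0.412) = 0.66. R² = 0.25 gives Φ(0.653) = 0.74.

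The gain over no adjustment is therefore about 3 to 4 points for R² = 0.09, and 10 to 12 for R² = 0.25. The simulated gain for r = 0.5 is slightly smaller (8 to 9 points), because this formula ignores lost degrees of freedom and chance imbalance.

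**5. Separating a different effect.** Take a true effect of 0.40 SD and assume a baseline–follow-up correlation of 0.6. The change score has SD √(2 × 0.4) = 0.894, so d = 0.447 and power ≈ Φ(2.530 − 1.96) = 0.72. ANCOVA on the baseline value alone has residual SD √(1 − 0.36) = 0.8, so d = 0.50 and power ≈ 0.81. That step of about 9 points involves no choice of other covariates.

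**The case against.** The strongest reply is that the main comparison is a covariate-free t test on change, so neither rule touches it. The screen belongs to an ANCOVA meant to show what shapes the outcomes, and screening is tolerable in an exploratory predictor model. Site is fixed in any case, and the baseline value already enters through the change score or the repeated measures. Much of this stands, and it confines the screening criticism to that ANCOVA. It does not rescue the baseline-test rule, which is written for the outcome analyses without exception and would have to displace or supplement the t test whenever a variable is flagged.

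A second reply is that the screen may be an ordinary collinearity check that keeps one of each correlated pair. That reading is possible and would drop fewer variables than the strict one simulated. The choice would still depend on the data.

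Third, type I error holds. That is conceded.

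Two stronger readings are tempting and should be resisted. Because the program targets self-efficacy and measures it again at 6 months, a reader might infer that the 6-month value would be adjusted for, removing part of the effect. The article does not say so. It lists self-efficacy beside age, gender, diabetes duration and comorbidity, which points to a baseline characteristic, and the timing of a covariate is a detail an article may leave to fuller documents. A reader might also credit covariate selection with the whole power gap between a change-score t test and a fully adjusted ANCOVA. Step 5 shows that, on its assumed correlation, much of such a gap comes from conditioning on the baseline value.

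**Conclusion.** The concern holds in a limited form. The article states, rather than leaves open, a rule that adjusts outcome analyses for chance baseline imbalances. That rule ignores prognostic value, omits a prognostic covariate about 95% of the time, and does not fit the t test named first. The ANCOVA screen adds outcome-dependent selection that can drop correlated prognostic variables and can conflict with the first rule, but only in an analysis that Table 2 calls exploratory.

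The validity of the test is not threatened: simulated type I error stayed at 0.039 to 0.051. The harm is a treatment-effect model settled after the data are seen, plus lost precision. In the simulation, the baseline-test rule gained at most about 1.5 points over no adjustment. Against a fixed set, the loss is a few points for a weakly prognostic covariate and can exceed 10 when covariates explain about a quarter of the variance. With uncorrelated covariates the screen itself loses about 1 point or less.

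The correlations, the number of baseline tests and the strict reading of the screen are assumptions. The figures also use 80 per group from Sample size; a larger enrolment would raise all the powers and shrink the gaps. The point deserves correction but does not undermine the trial.

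**What to change.** 1. Delete the baseline significance tests, the aim of confirming equality, and the sentence "Significant differences will be adjusted for in the outcomes analyses". Describe baseline characteristics by arm only.
2. For any adjusted estimate of the treatment effect, use one set fixed in advance: site, the baseline value of the outcome, age, gender, duration of diabetes, comorbidity level and baseline (T1) self-efficacy. Where the model already treats the baseline measurement as a repeated response, it need not be entered again as a covariate.
3. Report adjustment for any other variable, including a chance imbalance, as a labelled sensitivity analysis.
4. Keep bivariate screening, if at all, for the exploratory predictor model, and say that this model does not supply the treatment-effect estimate.

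The cost is a change of analysis wording, best made before outcome data are examined. It needs no extra participants or measurements, since every variable named is already a planned baseline item, and it removes a round of testing.

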#### Analysis of clinical effectiveness

##### Outcome measures

Table 2 describes the primary and secondary outcome measures used to evaluate clinical effectiveness. The primary outcome is the change in Physical Component Summary (PCS-12) score from the short form-12v2 health survey (SF-12) [58]. The SF-12 is a generic quality-of-life instrument that is well-validated and able to distinguish between groups of clients with known clinical differences in a variety of populations [58]. The pilot study supported the selection of the PCS-12 score as the primary outcome by demonstrating that the PCS-12 was responsive over the 6-month intervention period and grounded in questions that were easily interpreted by the older adult clients [43]. The PCS-12 is also a common primary outcome in studies evaluating programs similar to ours [59] and focuses on an outcome (physical functional ability) that is important to clients [60]. Secondary outcomes include the change in the following variables from baseline (*T*
_1_) to 6 months (*T*
_2_): Mental Component Summary (MCS) score from SF-12 [61]; Center for Epidemiological Studies Depression Scale (CES-D-10) [62–65]; Generalized Anxiety Disorder 7-item scale (GAD-7) [66–70]; Summary of Diabetes Self Care Activities (SDSCA) [71, 72]; and the Modified Caregiver Strain Index (CSI) [73].

**Table 2 Tab2:** Effectiveness outcomes, target population, and analysis

Effectiveness outcomes				
Variable/outcome	Hypothesis	Measure	Group(s)^a^	Method of analysis
Physical functioning	Improve more in the intervention group	Physical Component Summary (PCS-12) [58]	CT, CG	Means and standard deviations, *t* tests for comparing change from baseline (*T* _1_) to 6 months (*T* _2_) in the intervention and control groups ANCOVA analysis to explore predictors of primary outcome multiple regression with backward selection to explore impact of dose on primary outcome
Mental functioning	Improve more in the intervention group	Mental Component Summary (MCS) from SF-12 [61]	CT, CG	
Depressive symptoms	Larger reduction in the intervention group	Center for Epidemiological Studies Depression Scale (CES-D-10) [62–65]	CT, CG	
Anxiety	Larger reduction in the intervention group	Generalized Anxiety Disorder 7-item Scale (GAD-7) [66–70]	CT	
Self-management	More improvement in the intervention group	Summary of Diabetes Self Care Activities (SDSCA) [71, 72]	CT	

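### The primary comparison is a t test on change in PCS-12 that neither conditions on baseline nor includes site: valid, but inefficient, and adjusted only if baseline tests are significant

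*Protocol article*

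**What the plan says.** Under Outcome measures: "The primary outcome is the change in Physical Component Summary (PCS-12) score from the short form-12v2 health survey (SF-12"). Under Analysis of participants, t "tests will be used to compare the changes in primary and secondary outcomes from baseline" to 6 months in the two groups. Table 2 lists the same t test for comparing change and gives ANCOVA a separate purpose: "ANCOVA analysis to explore predictors of primary outcome".

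The text then describes a second model: "Primary and secondary measures will also be analyzed using repeated measures ANCOVA (two time periods) to understand the factors shaping these outcomes". For that model, "Site will be included as a predictor, consistent with our randomization strategy which stratified by site". The further candidates do not include baseline PCS-12: "Other potential covariates include age, gender, self-efficacy, duration of diabetes, and level of comorbidity". They are screened by bivariate analyses.

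The same section has the arms compared on baseline demographic and clinical characteristics by significance tests. Any characteristic that differs significantly is then to be adjusted for when outcomes are analysed.

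Randomization design explains the stratification: "to minimize the confounding effects of possible differences among the study sites, the sites will be used as a stratum". For subgroups, "The models will use the PCS-12 score for the dependent variable and independent variables will include group assignment, client characteristic" and the interaction. Neither baseline PCS-12 nor site is named there.

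**The concern.** Baseline PCS-12 is measured before randomization in every client and is likely to be the strongest predictor of the 6-month score. The named comparison uses it only through subtraction. That costs precision whenever r is below 1, and it over-corrects a chance baseline difference, because regression to the mean makes the arm that starts higher tend to gain less.

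The article's other provisions do not supply the missing adjustment. The ANCOVA is for explanation. The adjustment rule cannot be applied within a two-sample t test, so invoking it means moving to an unspecified model, and whether that happens depends on baseline p values. A baseline difference that narrowly misses significance stays unadjusted. The pilot effect (0.40) was below the planning effect (0.50), so the lost power is worth having.

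**Working it through.** **Inputs from the article.** Sample size: effect size 0.50, 5% alpha, 80% power, 20% attrition, 80 per arm, pilot effect 0.40, and an MID of about 3.0 points equal to 0.30 SD, hence SD of about 10. Analysis of participants: two-sided tests. Program implementation strategy: seven sites. **Assumed:** r, equal SDs at the two times, and the share of outcome variance explained by site.

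**1. The plan's own figure.** n per arm = 2(1.96 + 0.842)²/0.50² = 62.8, so 63 (64 with the t distribution). Dividing by 0.80 gives 79 to 80. The stated 80 per arm reproduces for an unadjusted t test and leaves 80 × 0.80 = 64 completers per arm.

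**2. Variance.** In units of the score variance, the change score has 2(1 − r) and the ANCOVA residual 1 − r². The ratio is (1 + r)/2: 0.75, 0.80, 0.85 and 0.90 at r = 0.5, 0.6, 0.7 and 0.8.

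**3. Power at 64 per arm.** Power = Φ(δ/(s√(2/64)) − 1.96), with √(2/64) = 0.177. The article does not say whether its effect size is in SDs of the change or of the score, so both are shown.

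| Effect | r | t test on change | ANCOVA |
|---|---|---|---|
| 0.50 change SDs | 0.5 | 80.7% | 90.4% |
| 0.50 change SDs | 0.6 | 80.7% | 88.5% |
| 0.50 change SDs | 0.7 | 80.7% | 86.6% |
| 0.50 change SDs | 0.8 | 80.7% | 84.6% |
| 0.50 score SDs | 0.5 | 80.7% | 90.4% |
| 0.50 score SDs | 0.6 | 88.5% | 94.2% |
| 0.50 score SDs | 0.7 | 95.5% | 97.7% |
| 0.40 score SDs (pilot) | 0.5 | 61.9% | 74.3% |
| 0.40 score SDs (pilot) | 0.6 | 71.6% | 80.7% |
| 0.40 score SDs (pilot) | 0.7 | 83.2% | 88.7% |

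Simulation at 0.40 score SDs (r = 0.5, 0.6, 0.7) gave 62.5%, 70.8% and 83.9% for the t test against 74.0%, 79.4% and 88.4% for ANCOVA. Type I error was 4.5% to 5.8% across the two methods.

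**4. Chance imbalance.** A baseline difference d shifts the change-score estimate by −(1 − r)d. A difference at the edge of significance is 1.96 × 0.177 = 0.35 SD. The shift is then −0.17, −0.14 and −0.10 SD at r = 0.5, 0.6 and 0.7. With SD 10 that is about 1.7, 1.4 and 1.0 points, against an MID of 3.0.

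**5. Site.** If site explains 1% to 10% of the variance, power at 0.50 SD is 80.9% to 82.0% without site and 81.1% to 84.6% with it. The largest gap is 84.6 − 82.0 = 2.6 points. The true alpha of the unadjusted test is 0.049 to 0.039, which is slightly conservative.

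**6. The repeated measures model.** With two periods, complete data and baseline treated as an outcome, the group-by-time contrast is (follow-up mean − baseline mean) in one arm minus the same in the other. That is the difference in mean change, and a site main effect does not alter it.

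**The case against.** The strongest reply is that the plan is coherent as it stands. The trial was sized for an unadjusted t test, the size reproduces, and the test holds its error rate. Table 2 ranks the analyses, with the t test for comparison and ANCOVA for exploration. Site is modelled, and an adjustment rule exists. Much of this stands, and it rules out several stronger readings that a reader might infer:

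- **That baseline is ignored and imbalance left uncorrected.** Subtraction uses baseline; the fault is over-correction.
- **That the test is invalid, or that omitting site inflates error.** Steps 3 and 5 show otherwise.
- **That the t test and ANCOVA compete as unranked primary analyses.** Their stated purposes differ. What remains open is the adjustment rule, which can change the outcome model after the data are seen.
- **That large baseline differences would go unadjusted.** A significant one might trigger the rule, although the rule speaks of demographic and clinical characteristics, and whether PCS-12 counts is arguable.

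Two further points limit the case. A repeated measures model that constrains the baseline means to be equal would recover baseline adjustment, and the article does not specify how baseline enters. The listed subgroup terms may also not be exhaustive. A fuller plan could settle both. Neither changes the comparison that the article does fix.

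**Conclusion.** The point holds as a should-fix on efficiency and prespecification. At the planning effect in change-score SDs, conditioning on baseline is worth about 4 to 10 power points for r from 0.8 to 0.5. At the pilot effect in score SDs it is worth about 12, 9 and 5 points at r = 0.5, 0.6 and 0.7. A baseline difference just short of significance would move the change-score estimate by 0.10 to 0.17 SD for r from 0.7 to 0.5, and the plan's rule would leave it there. Site contributes under 3 power points even at 10% of variance.

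These figures rest on assumed r and on 80 per arm. The Abstract gives 160 participants in total, while Participants and setting gives 160 in each province. If the latter is meant and the provinces are pooled, 128 completers per arm give the t test 97.9% power at 0.50, and the gain is smaller.

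**What to change.** Name one primary analysis: a linear model of 6-month PCS-12 on arm, baseline PCS-12 and site, reporting the arm coefficient with its 95% confidence interval. With baseline as a covariate, the arm coefficient is the same whether the dependent variable is the 6-month score or the change, so the primary outcome need not be redefined.

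- Use the same form for each secondary client outcome, with its own baseline.
- Add baseline PCS-12 and site to the subgroup interaction models.
- Delete the significance-triggered adjustment; otherwise the primary model could still change with the data.
- Keep the t test on change as a supportive, unadjusted result, and keep the ANCOVA with screened covariates as explanatory.
- Align Table 2 with the text.

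The cost is analysis wording only. Every variable is already collected, and seven sites add six terms. The sample size need not change.

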### Participants and setting

A strategic first step for this study was the development of a partnership between researchers in the Aging, Community and Health Research Unit (ACHRU) at McMaster University (Hamilton, ON, Canada) and the University of Alberta (Edmonton, AB, Canada), program coordinators from seven community-based organizations, and seven diabetes education centers (Ontario) or primary care networks (Alberta). The study will enroll 160 participants in each of two Canadian provinces, Ontario and Alberta. Although these provinces are in the same country, they encompass diverse characteristics in terms of geography (Ontario is in the east, Alberta the west), culture, and health care system structure. In Ontario, study participants will be recruited from clients who have been recently referred for diabetes-related services to diabetes education centers (DECs). DECs are regional centers that provide ongoing diabetes education programs, counselling and follow-up sessions by registered nurses (RNs) and registered dietitians (RDs) for clients and their families. In Alberta, study participants will be recruited from clients who have been recently referred to diabetes or chronic disease management programs at three primary care networks (PCNs). PCNs are centralized resource facilities that provide equipment and health care teams to service clients from physician clinics in close proximity to one another. The Ontario and Alberta provinces were selected to compare and contrast different health care systems. The specific sites within each province were selected because they serve a large and growing older adult population, and demonstrated strong support for the program. Community partner organizations were selected and invited based on existing collaborations with the sites and/or interest in health promotion for community-dwelling older adults. The community partners were also selected based on availability and accessibility of an appropriate space to host monthly group program sessions and availability of staff members to participate in program delivery (e.g., a program coordinator for the group sessions).

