### Participant flow, assessments and timeline

The study involves two assessments: one at baseline (*T*
_1_) and the other 6 months after baseline (*T*
_2_). At baseline, data will be collected on demographic, clinical, and socioeconomic variables in addition to assessment of the primary and secondary outcome variables. The flow of participants through the study phases will be presented using a flow diagram which conforms to the Consolidated Standards of Reporting Trials (CONSORT) guidelines [55] for pragmatic trial reporting (Fig. 3).

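### The subgroup models list no baseline PCS-12 term and use an outcome not aligned with the primary one; on the natural reading they are unbiased but less precise than the collected data allow

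*Protocol article*

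**What the plan says.** The article describes PCS-12 as an outcome in three ways.

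- **Outcome measures:** "The primary outcome is the change in Physical Component Summary (PCS-12) score from the short form-12v2 health survey (SF-12"). Under Analysis of participants, the main client comparison is accordingly a t test on changes, supported by a repeated measures ANCOVA over the two time periods with site as a predictor.
- **Analysis of participants, dose paragraph:** the primary outcome variable is identified as the PCS-12 score at 6 months.
- **Analysis of participants, subgroup paragraph:** "The models will use the PCS-12 score for the dependent variable and independent variables will include group assignment, client characteristic", and the interaction term. No time point, change score, baseline PCS-12 or site is named.

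The baseline value will be available for every client: "At baseline, data will be collected on demographic, clinical, and socioeconomic variables in addition to assessment of the primary and secondary outcome variables". The only general provision for adjustment is in the baseline-comparison paragraph, where variables that differ significantly between the arms are carried into the outcome analyses.

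**The concern.** Finding out who benefits most is objective 2, and the Discussion presents the answer as a guide for directing scarce resources. A test of interaction needs far more information than a test of the main effect, so precision matters most here. Yet the model is written without the one covariate likely to explain much of the outcome's variance, although that covariate is measured on everyone before randomization. The dependent variable is also described differently from the primary outcome, so two analysts could fit different models and both claim to follow the plan. What is at stake is a wider confidence interval and a greater chance of missing a real subgroup difference, together with an avoidable ambiguity about which model was planned.

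**Working it through.** **1. Inputs from the article.** Two-sided 0.05 ("All statistical tests will be performed using two-sided tests at the 0.05 significance level"). Design assumptions: "We based our estimate of the sample size on an effect size of 0.50, 5% alpha, 80% power and 20% attrition". Result: "the sample size was 80 (each) for the intervention and control groups". Allocation: "using a 1:1 allocation ratio". The Participants and setting section says "The study will enroll 160 participants in each of two Canadian provinces, Ontario and Alberta", which would make 320 in total, so both sizes are carried.

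**2. The plan's own figure.** For a 0.50 SD difference, 80% power and two-sided 5%, the t-based calculation gives 64 per arm, and 64/0.8 = 80. The normal approximation gives 63, and 63/0.8 rounds up to 79. The stated 80 per arm is reproduced. Completers are 160 × 0.8 = 128, or 320 × 0.8 = 256.

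**3. Assumptions that the article does not supply.**
- The characteristic splits clients 50:50.
- The interaction is 0.5 SD. This borrows the size of the planned main effect; no interaction size is stated.
- r, the baseline to 6-month correlation of PCS-12, is varied from 0.3 to 0.7.
- The effect of adding site is ignored.

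**4. Formulas.** In units of the 6-month SD, the unadjusted interaction has SE = 4/√N:
- N = 128: 4/√128 = 0.354
- N = 256: 4/√256 = 0.250

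The residual variance relative to the unadjusted 6-month score is 1 − r² with baseline as a covariate and 2(1 − r) for the change score, so the SE is multiplied by the square root of that factor. Power comes from the noncentral t distribution.

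**5. Results.**

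| Model | Relative variance | SE, N = 128 | Power, N = 128 | Power, N = 256 |
|---|---|---|---|---|
| 6-month score, unadjusted | 1 | 0.354 | 29% | 51% |
| Baseline-adjusted, r = 0.3 | 0.91 | 0.337 | 31% | 55% |
| Baseline-adjusted, r = 0.5 | 0.75 | 0.306 | 37% | 63% |
| Baseline-adjusted, r = 0.6 | 0.64 | 0.283 | 42% | 70% |
| Baseline-adjusted, r = 0.7 | 0.51 | 0.252 | 50% | 80% |

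The variance penalty for leaving baseline out is 1/(1 − r²): 1.10 at r = 0.3, 1.33 at 0.5, 1.56 at 0.6 and 1.96 at 0.7.

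**6. Comparison with the change score.** At N = 128 the change score gives 22% power at r = 0.3, 29% at 0.5 and 44% at 0.7, against 29% for the unadjusted 6-month score throughout. The 6-month score is weaker than change only when r exceeds 0.5.

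**7. Validity check.** Simulation with 64 completers per arm and no interaction gave rejection rates of 4.4% to 5.7% for the three models (6-month, change, baseline-adjusted) at r = 0.3, 0.5 and 0.7. All three keep the nominal level.

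**The case against.** **The sentence is condensed.** It gives no time point, and its list of predictors is introduced as what the models include, not as a closed list. PCS-12 score could be shorthand for the primary outcome, as it is elsewhere in the Outcome measures section, and a full covariate list may sit in a document not shown. This stands in part: the unadjusted 6-month score is a reading and not a certainty. But the article does write out the dependent variable and the model terms, and the paragraph just before it names the 6-month score as the primary outcome variable. The conflict with the change definition is in the text itself.

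**Adjustment for significant baseline differences might bring baseline PCS-12 in.** Only by chance: it depends on a significant difference between the arms, and a useful covariate need not be imbalanced.

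**Three stronger readings are tempting, and the documents do not support them.**
- *A different estimand.* A reader might infer that a 6-month score answers a different question from change. Under randomization the arms have equal expected baseline within each level of a baseline characteristic, so the two interactions have the same expected value.
- *Chance baseline imbalance as a separate harm.* It is already part of the standard error and confidence interval of the unadjusted interaction. Counting it next to the power loss counts it twice.
- *Inflated false positives from entering both visits as independent records.* Nothing in the article proposes this; where two time periods are analysed together, a repeated measures model is named.

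**The test stays weak after adjustment.** True at 128 completers: even at r = 0.7 power is only about 50%. Adjustment is not a cure, but the gain is free.

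**Conclusion.** The point holds as one of efficiency and consistency, not of validity. The primary outcome is change in one section and the 6-month score in another, and the subgroup outcome has no time point and no baseline term. On the most natural reading, the interaction variance is 1.10 to 1.96 times what it could be for r between 0.3 and 0.7. Relative to a baseline-adjusted model the loss exists at any non-zero r, apart from the one degree of freedom spent. Relative to the change score it exists only if r exceeds 0.5, so switching to change alone would not be a safe remedy.

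The power figures rest on an assumed correlation, an even split and a borrowed interaction size; other values would move them. The matter is confined to a secondary objective, because the main comparison and its supporting analysis do use both measurements. It is a free improvement worth making before analysis.

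**What to change.** Replace the subgroup sentence with a complete model: PCS-12 at 6 months regressed on baseline PCS-12, site, group, characteristic and group-by-characteristic, with one record per client. Report each interaction estimate with its 95% confidence interval. Use one definition of the primary outcome in the Outcome measures section, the dose analysis and the subgroup analysis.

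Cost: a few sentences of wording. Baseline PCS-12 is already collected and site is already the randomization stratum, so no new data, visits or participants are needed.
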